### Strategies to improve adherence to interventions {11c}

While in-patient, trial staff will review all participants daily and ensure they are adherent to their prescribed medication, both standard care and corticosteroids where relevant. At discharge, participants will be advised to complete their medication as prescribed. Because of the pragmatic nature of the trial, trial staff will not conduct any procedures to monitor and/or improve adherence to treatment after discharge.

### Relevant concomitant care permitted or prohibited during the trial {11d}

There is no specific concomitant care prohibited during participation in the trial. All of the care for the participants will be as determined by the treating physicians.

Participants enrolled into the trial will not be permitted to co-enrol in other interventional studies during their 30-days of participation. Participation in studies that do not involve an intervention, that is, observational studies, is acceptable.

### Provisions for post-trial care {30}

The trial intervention, low-dose oral corticosteroids, have in been in clinical use for a long time. At the doses being given to trial participants, they are not likely to cause long-term harm to participants. If a participant reports a suspected unexpected serious adverse event (SUSAR) that is deemed to be causally related to their participation in the trial, the trial will provide care for the participant until resolution of symptoms. Such cases will be reported to ethics and regulatory committees as well as the sponsor.

### Outcomes {12}

The primary outcome for the trial will be mortality at 30 days after randomization. This will be recorded as ‘dead or alive’.

Secondary outcomes will be:

Mortality at 7,14- and 21-days following randomizationIn-hospital mortality compared to mortality after discharge from hospital (up to 30 days post randomization)Correlation of pre-existing and treatment induced changes in the participants’ immune and metabolic profiles with study outcomes

Other descriptive results will be described such as duration of hospital stay, admission to ICU/referral to higher level hospital and serious adverse events as reported by the clinical teams and patients on follow-up phone calls, bearing in mind the pragmatic nature of the trial.

### Participant timeline {13}

All participants enrolled in the trial will be reviewed once daily while in-patient by a member of the study team. During these reviews, data on clinical progress will be recorded. The data collected will include documentation of antibiotics and other treatments that the patient is receiving.

After discharge, a member of the study team will make a phone call to the participant or their next of kin (where a participant is not reachable on their personal phone) on day 14 and day 30 post randomization to find out how the patient is doing including whether readmitted to a hospital, fully recovered or if the participant has died.

During the telephone follow-up, data on the results of any additional tests performed and/or medications received after the hospitalization will also be collected. If the patient is reported to be deceased, the date of death and cause of death (where available) will be recorded.

There will be no further follow up after day 30 post randomization into the study.

### Sample size {14}

The primary hypothesis is that adjunct corticosteroid treatment will reduce mortality in the intervention arm by ~25% (relative measure). This is a conservative measure as the studies described in the background report relative risk reductions of between 33% and 61%. Observational data indicates 30% in-hospital mortality among based on data collected from CIN hospitals in the past one year and Kilifi County Hospital over a period of 5 years
^
24
^. We have made a conservative assumption that 30-day mortality in the control arm of the trial will be 20% and that 30-day mortality in the intervention arm will be 15%. Allowing for 5% loss to follow-up, a sample size of 1,090 patients per study arm (total 2,180 patients, ~ 390 deaths) will achieve statistical power of 85%, with a 2-sided type 1 error rate of 5%.

### Recruitment {15}

Study clinicians will work with admitting clinicians at the outpatient departments, admissions area in the ward, and nursing teams at the medical wards to ensure they are informed of all patients admitted with respiratory illness. They will then screen these patients for eligibility for the trial and enrol those who provide written informed consent. A window period of 48 hours between admission and recruitment will be implemented to allow study clinicians adequate time to identify all eligible participants (
Table 2).

**Table 2. T2:** Summary of trial activities. This table summarises trial activities and procedures being conducted once a participant is recruited into the trial.

Study Day	Day of recruitment (Day 0)	During Hospitalization	After hospital discharge
Confirm eligibility	x		
Obtain written informed consent	x		
Randomization	x		
Patient issued with study number and a random treatment allocation	x		
Study Intervention (Standard care alone or standard care plus corticosteroid)	x	Daily for up to 10 days ^ a ^	x ^ a ^
Follow-up phone call			Day 14 Day 30
Data Collection	x	x	x
Adverse events		x	x
Blood samples ^ b ^	x	x ^ b ^	

^a^ If patient is discharged before 10 days, they will continue with corticosteroid medication as an outpatient until day 10.
^b^ Blood samples will only be collected from 100 randomly selected participants (50 in each arm) on day 0,1,2 and 3

## Assignment of interventions: allocation

### Sequence generation {16a}

Once eligibility has been confirmed and informed consent provided, all patients will be randomized to receive either:

a) Standard of care, OR,

b) Standard of care plus adjunctive low-dose corticosteroids for 10 days

The random allocation sequence will be computer-generated at the KEMRI-Wellcome Trust Research Programme according to a block randomization list of random block sizes for each site.

### Concealment mechanism {16b}

At each site, printed and sealed sequential randomization cards will be used for treatment allocation. The envelopes will be numbered in a sequential order to prevent out of order randomization and each study site will have a unique set of randomization cards numbered from the first to the last.

### Implementation {16c}

The site clinician will conduct randomization using the next numbered sealed opaque envelope. To avoid out-of-order treatment allocation due to bias, the randomization number, enrollment number and time of enrollment of each participant will be counterchecked with a master list during ad hoc data checks.

Blinding of allocation and treatment outcome will not be possible in this open label trial. This limitation is however mitigated by the objective nature of mortality as a primary outcome.

## Assignment of interventions: Blinding

### Who will be blinded {17a}

This is an open-label pragmatic trial and blinding is not relevant.

### Procedure for unblinding if needed {17b}

This is an open-label pragmatic trial and blinding is not relevant.

## Data collection and management

### Plans for assessment and collection of outcomes {18a}

Trial staff will be trained on data quality and the necessary data to be collected for trial participants. Basic sociodemographic and clinical data for the participants will be collected from their medical records while in the hospital.

The trial staff will not conduct additional medical assessments but will record findings from assessment done the attending clinical team.

The main trial outcome is vital status (dead or alive) at 30 days after enrolment. Outcome data will be collected via phone call if the participant will have been discharged from the hospital. For participants who are still in-patient by the 30
^th^ day of participation, outcome data will be recorded on the same day in-person.

Data will be abstracted on to electronic case report forms (eCRFs). Regular data checks will be conducted on the database to ensure completeness of the data.

### Plans to promote participant retention and complete follow-up {18b}

The study clinician will review participants daily while in-patient to ensure adherence to prescribed medication and solicit for adverse events. After discharge, participants will be contacted on their 14
^th^ and 30
^th^ day of participation. To do this, at least three different contact details for each participant will be collected. Additionally, the study team will record dates and frequency of visits to regular clinics at the study site e.g., cardiac clinic, diabetes clinic etc., that the participant attends to help with tracing.

Participants will be encouraged to reach out to the study team at any time during their participation if they have health related concerns or questions.

### Data management {19}

Data will be directly entered into electronic CRFs in an electronic database. The database is compliant with Good Clinical Data Management guidelines and 21 Code of Federal Regulations (CFR) Part 11 regulations on clinical data management systems for use in clinical trials. Data entry will be done via secure web interface with range and logic checks used to ensure data quality.

Fully encrypted password protected computers and/or mobile devices, for example, tablets will be used for data entry or paper forms where data cannot be entered directly into the eCRF. Management and maintenance of computers will lie with the clinical teams at the study site with remote support from central study team based at KEMRI.

The database will be kept in a locked server-room. Only the system administrators have direct access to the server and back-ups and passwords are required for access to the system and database.

All data entered into the eCRFs have identifiers that identifying the user who entered the data with the exact time and date. Retrospective alterations of data in the database are recorded in an inbuilt audit function. Time, table, data field and altered value, and the person are recorded. Logical queries developed using R-scripts will be run on the database to check for missing data or entry errors. Identified errors will be resolved by the study team.

Back-ups of the whole system including the database will be run internally several times per day. Back-ups will be stored in a secure location. Paper records will be kept in locked cabinets at the study sites.

Source documentation will be held securely at the participating study sites. Access will be granted to monitors responsible for quality assurance, for data entry staff and for purposes of medical care. Access will also be granted for audit by statutory authorities and others. Non-study team members will not be granted access. Qualified staff will supervise data collection and entry on a regular basis.

### Confidentiality {27}

Paper based clinical records will be kept in locked cabinets in the participating facilities and subsequently at KEMRI- CGMR-Coast. All electronic data, including immunological data will be kept in anonymized databases linked by a unique participant identification number to clinical data.

After the trial ends and statistical analysis is conducted, a clean final database(s) of de-identified individual-level clinical, laboratory and safety data will be produced by KEMRI-CGMR-Coast. This will be available on request for further analysis by other researchers.

### Plans for collection, laboratory evaluation and storage of biological specimens for genetic or molecular analysis in this trial/future use {33}

Of the 10ml venous blood drawn from each patient for each time point, 0.5ml of the blood sample will be used to conduct a full blood count. The remaining sample will be used for whole blood transcriptome analysis and to obtain plasma and peripheral blood mononuclear cells (PBMCs) for immunology work.

A series of cellular and serological assays will be used to characterize the immunological and metabolic status of the participants. RNA will be purified, and libraries constructed and sequenced using the Novagene platform available at a collaborating laboratory in Kenya. The sequence data will be analyzed in R. EdgeR (
https://doi.org/10.1093/bioinformatics/btp616) will be used to determine genes differentially expressed between those who died and those who recovered following treatment with or without steroid administration to determine biomarkers predictive of the outcome of the treatment. The differentially expressed genes will also be used to determine, bioinformatically, before treatment immunological status associated with the outcome of the trial. The transcriptome profile from before, during and after treatment will also be compared to determine genes up- or down-regulated following treatment and the calculated fold change will be related to the outcome and used to understand the immunological response correlated with the outcome of the trial.

The stored PBMCs will be used to phenotype in detail the cellular immune status in the trial arms before, during and after treatment using flow cytometry. Specifically, the frequency of B-cells, CD4, CD8, Natural killer (NK) cells, gamma delta (
**γ** T cells) will be described. The CD4 T cell will be further categorized into Th1, Th2, Th17 as determined by expression of IFN-
**γ**, IL-4 and IL-17 through intracellular staining and flow cytometry. The cellular immune phenotype data along with blood count data will be correlated to the outcome of the trial and will facilitate interpretation of the whole blood transcriptome data obtained above. This data will be integrated with the phenotypic and transcriptomic data to understand immune and biological pathways associated with the outcome of the trial.

The stored plasma will be used to characterize, at proteomic and metabolic level, the global immune and metabolic status before treatment and changes induced following treatment. Luminex platform will be used to quantify specific cytokines using commercial kits such as the 34-plex human ProcartaPlex from Thermo Fisher Scientific that contain multiple targets that have been associated with Pneumonia including SARS-CoV-2 related pneumonia. We will also quantify a range of growth factors such as Insulin-like growth factor 1 (IGF-1)
^
25
^, IGF binding proteins such as IGFBP1-6 and GDF-15
^
26
^ that have been shown to influence host survival under adverse conditions. 

In addition to the targeted approach, untargeted mass spectrometry approach will be used, a facility that is available at KEMRI-CGMRC. Using this approach, we identified upregulation of IGF-1 binding protein 2 (IGFBP2) that functionally inhibits IGF- and inflammation
^
27
^ to be associated with the risk of early death in sick malnourished children. Both before and after treatment samples for each participant will be subject to targeted and untargeted analysis and analysed as described for the whole transcriptome data to identify protein/metabolite biomarker(s) predictive of the outcome of the trial and the immunological and metabolic processes relevant to the outcome. Samples will be stored for future use according to KEMRI guidelines and consent for this will be sought from the participants sampled.

Samples will be stored for future use according to KEMRI guidelines and consent for this will be sought from the participants sampled.

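### Genes selected on died versus recovered are reused in the same roughly 100 participants to characterise pre-treatment status linked to that outcome, so any association read from the second step is optimistic

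*Protocol article*

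**What the plan says.** Section {33} of the Protocol article sets out two linked steps for the transcriptome data. First, edgeR is used to find "genes differentially expressed between those who died and those who recovered following treatment with or without steroid administration to determine biomarkers predictive of the outcome". Second, the genes found in this way are carried forward: "The differentially expressed genes will also be used to determine, bioinformatically, before treatment immunological status associated with the outcome of the trial". Plasma assays, targeted and untargeted, are to be analysed in the same manner as the transcriptome "to identify protein/metabolite biomarker(s) predictive of the outcome of the trial".

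Trial design {8} and the footnote to Table 2 limit blood sampling to about 50 participants per arm, at enrolment and at 24, 48 and 72 hours. Pre-existing immune and metabolic profiles are part of a named secondary objective (Objectives {7}) and a named secondary outcome (Outcomes {12}).

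Statistical methods {20a} refers back to section {33}. It adds a multinomial mixed model for genes or proteins that change over the first 72 hours, with death or survival in each arm as the categories, and a functional analysis of the significant features.

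**The concern.** The two steps use the same outcome and the same people. A feature that enters the list because it separated deaths from recoveries has already been favoured by chance in that direction. Asking whether the listed features are linked to death at baseline in those participants is therefore not an independent question. If selection used the enrolment samples, the second look repeats the first. If selection used a later sample, a person's expression at 24 to 72 hours is likely to be correlated with expression at enrolment, and the chance part of the association carries back.

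The word *predictive* adds to this. A contrast of deaths with recoveries shows prognosis. A claim that a marker predicts response to corticosteroids needs its association with death to differ by arm.

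At stake is the pre-existing-profile part of the immunology objective: a baseline signature could look stronger than the data support.

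**Working it through.** **1. The plan's own figures.** Sample size {14} gives the planning rates: "30-day mortality in the control arm of the trial will be 20" per cent and "30-day mortality in the intervention arm will be 15" per cent, with 85% power and two-sided 5% error. With p̄ = 0.175:

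n = [1.960·√(2·0.175·0.825) + 1.036·√(0.20·0.80 + 0.15·0.85)]² / 0.05² = 1,035.5, so 1,036 per arm. Dividing by 0.95 for loss to follow-up gives 1,091, against 1,090 stated. Deaths: 1,090 × (0.20 + 0.15) = 381.5, against about 390 stated. The planning rates are thus confirmed as the basis of the design. The article gives no corresponding figure for the immunology analysis.

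**2. Deaths in the sub-study.** 50 × 0.20 + 50 × 0.15 = 17.5, about 18. At the 30% in-hospital mortality that Sample size {14} reports from observational data, 100 × 0.30 = 30.

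**3. Error rate per gene when selection uses a later sample.** Take a gene unrelated to death, with test statistics Z₁ (later sample) and Z₀ (enrolment) that are standard normal with correlation r. Assume selection at p<0.01, that is |Z₁| > 2.576. The chance that a nominal 5% baseline test then rejects is P(|Z₀| > 1.960 given |Z₁| > 2.576):

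| Assumed r | Rejection rate |
|---|---|
| 0 | 5% |
| 0.5 | 28% |
| 0.7 | 53% |

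This needs no assumption on the number of genes. The cut-off and r are assumptions.

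**4. A score built from selected genes, with no true signal.** Assumed: 100 participants, independent normal genes, t-tests in place of edgeR, and a signed score of the 20 genes with the smallest p-values.

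| Deaths | Genes | Where selected | Apparent baseline AUC | AUC with selection repeated in 5-fold cross-validation |
|---|---|---|---|---|
| 18 | 15,000 | same samples | 0.998 | 0.49 |
| 30 | 15,000 | same samples | 0.994 | 0.51 |
| 18 | 5,000 | same samples | 0.997 | 0.50 |
| 18 | 15,000 | later sample, r = 0.7 | 0.97 | 0.50 |
| 18 | 15,000 | later sample, r = 0.4 | 0.86 | 0.50 |
| 18 | 15,000 | later sample, r = 0 | 0.48 | 0.49 |

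A separate null simulation with a top-50 score, selection at a later sample and r from 0.3 to 0.7 included correlated genes. It gave apparent AUCs from 0.65 to 0.98, against 0.47 to 0.54 with selection inside cross-validation. The 0.98 came from independent genes at r = 0.5, so gene correlation matters a good deal.

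**5. With false-discovery control at selection.** Using Benjamini–Hochberg at 5% (18 deaths, 15,000 independent genes, same samples), 5.2% of 400 null data sets yielded any gene. In those, the selected genes showed an apparent AUC of about 0.84 where the truth is 0.5. Control of this kind makes false genes rare but does not remove the optimism in the size of association for those that pass.

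**The case against.** The strongest reply is that the article does not commit to the analysis that would be most biased. It promises no score, classifier or AUC. It does not say which sample the died-versus-recovered contrast uses. If that contrast is made on enrolment samples, across all genes with false-discovery control, it already is the right baseline test, and the reuse may be no more than pathway annotation. The word *bioinformatically* and the functional analysis in Statistical methods {20a} fit that reading. Thresholds and resampling are details that an analysis plan not shown may well set. All of this stands, and it limits the point to what happens if the second step is taken as evidence.

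Two stronger inferences are tempting and should not be drawn. One is that strong markers will appear even if no gene carries information. That requires a loose threshold or a fixed top list, evaluation in the same people, and correlated samples. The article fixes none of the thresholds or correlations, and false-discovery control would leave about 95% of null data sets with no gene at all. The other is that the markers will be presented as showing who benefits from corticosteroids. The text speaks of predicting the outcome of the treatment or of the trial, not benefit from steroids, and trial arm does enter through Objectives {7} and the multinomial model in {20a}. That model, however, is described for change over 72 hours, not for baseline status.

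What the reply does not remove is the route that section {33} states: a list chosen on the outcome is carried forward to characterise baseline status associated with that outcome, in the same participants.

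**Conclusion.** The point holds in conditional form. Read as a test of association or prediction, the second step is optimistic. The amount cannot be fixed from the article: it depends on the selection threshold, the within-person correlation and the correlation among genes, none of which is given. Under the assumptions shown, the 5% error rate per gene rises to 28% (r = 0.5) or 53% (r = 0.7), and null apparent AUCs range from about 0.5 when samples are uncorrelated to nearly 1 when the same samples serve both steps. With about 18 deaths (30 at the observed in-hospital rate) there is little information to offset this. The absence of a stated threshold or resampling scheme is not itself the finding. This is an inexpensive improvement to a secondary, mechanistic objective; the 30-day mortality comparison is not touched.

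**What to change.** - Determine pre-treatment association from the enrolment samples alone, across all measured genes, proteins and metabolites with false-discovery-rate control, and not on a set already selected on the outcome.
- If a signature or an accuracy measure is reported, repeat feature selection and fitting inside cross-validation and report the cross-validated AUC with its interval.
- Describe markers as associated or prognostic, and as hypothesis-generating given about 18 expected deaths. Keep *predictive* of treatment response for a marker supported by an arm-by-baseline-marker term.

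The cost is analysis wording and some computing time; no new samples are needed. The drawback is fewer markers and lower reported discrimination.

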## Trial design {8}

We will conduct a pragmatic open label randomized controlled clinical trial. Eligible participants will be recruited from the in-patient adult medical wards of the participating hospitals. Patients admitted to the general wards as well as the High Dependency Units (HDU) and Intensive Care Units (ICU) will be eligible to join the trial and will be identified by the attending clinician and a study clinician.

Participants enrolled into the trial will be randomized 1:1 to either receive standard of care for CAP or standard of care plus a 10-day course of low-dose oral corticosteroids. A subset of all recruited participants, about 50 per trial arm, will be further randomized to have a blood draw at four timepoints during their participation. For these participants, a 10 ml blood sample will be collected at enrollment, 24, 48 and 72 hours after enrollment for an immunology sub study.

All participants will be followed up to their 30
^th^ day after enrollment to determine their vital status. The median duration of hospital admission for patients with CAP in the participating hospitals is 4 days, therefore having the primary outcome ascertained at 30 days is unlikely to result in misclassification of patients where some are recorded as being alive only to die a few days later.

Being a pragmatic trial, the study will not interfere with any procedure, investigations, or treatments that the attending clinicians administer to participants. However, all treatments received will be recorded.

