### Intervention description {11a}

Trial participants will be randomized 1:1 to either of the two trial arms; standard care for community acquired pneumonia alone (control arm) or standard care plus a 10-day course of low-dose oral corticosteroids (intervention arm).

Participants randomized to the control arm will receive treatment according to local and WHO guidelines for CAP which currently recommend a beta lactam antibiotic and a macrolide for 7–14 days
^
22
^. In order to minimize variability in the standard treatment offered at the different hospitals, the study team will provide hard copies of the treatment guidelines, as we have demonstrated that this is associated with better adherence
^
23
^. In the event of stockouts of standard treatment, the trial will procure the medications for study patients as prescribed by the treating physician, and in accordance with trial treatment allocation. No further interventions will be made in this pragmatic clinical trial.

Participants who are randomized to the intervention arm will receive the standard care treatment for CAP as outlined above and any of the equivalent doses of corticosteroids listed in
Table 1 for a period of 10 days. The study will provide the corticosteroids for all participants in the intervention arm based on local availability. The corticosteroids will be administered orally, including via nasogastric tube for patients on ventilation or otherwise unable to take the medications orally.

**Table 1. T1:** Corticosteroids to be used in the trial. This table details the corticosteroids being used as the trial intervention. The corticosteroid doses represented in the table are bioequivalent.

Corticosteroid	Once daily dose
Dexamethasone	6mg
Betamethasone	5mg
Hydrocortisone	160mg
Methylprednisolone	30mg
Prednisolone	50mg
Prednisone	50mg

All other care will be determined by the clinical team primarily responsible for the patient’s care.

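### The immunology sub-study promises an after-treatment comparison, but its last planned sample falls at 72 hours of a 10-day course, and a complete-case rule for the serial samples would select on outcome

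*Protocol article*

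**What the plan says.** All of the following is in the Protocol article.

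- **Promised comparison.** Section {33} states: "The transcriptome profile from before, during and after treatment will also be compared to determine genes up- or down-regulated following treatment". The same section plans cell phenotyping by flow cytometry over the same three states. For plasma it adds: "Both before and after treatment samples for each participant will be subject to targeted and untargeted analysis".
- **Sampling.** Trial design {8} states: "a 10 ml blood sample will be collected at enrollment, 24, 48 and 72 hours after enrollment for an immunology sub study". Footnote b of Table 2 (Recruitment {15}) agrees: "Blood samples will only be collected from 100 randomly selected participants (50 in each arm) on day 0,1,2 and 3". The blood-sample row of that table is marked for day 0 and for the hospital stay; the cell for the period after discharge is empty. Participant timeline {13} describes contact after discharge by telephone only, on days 14 and 30.
- **Treatment length.** Intervention description {11a} gives 10 days of corticosteroid and 7 to 14 days of antibiotics. Footnote a of Table 2 has the corticosteroid continue at home to day 10 after an earlier discharge.
- **Length of stay.** Trial design {8} states: "The median duration of hospital admission for patients with CAP in the participating hospitals is 4 days". Recruitment {15} allows up to 48 hours between admission and recruitment.
- **Analysis.** Statistical methods {20a} models gene and protein change over the first 72 hours in a multinomial mixed model of survival by arm, and sets complete-case analysis for secondary endpoints. Section {20c} rules out imputation.

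**The concern.** There are two linked problems.

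First, {33} treats during and after treatment as different states and promises to compare them. The schedule yields samples only before and during treatment. A report that follows {33} literally would label a day-3, on-drug sample as after treatment and could draw conclusions about recovery or post-steroid immune state that no planned sample can support.

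Second, the later samples depend on the participant still being in hospital. A participant who dies before 72 hours has no sample, and none is scheduled for one who goes home earlier. The sub-study relates immune change to survival. If only complete series are analysed, early deaths and quick recoveries drop out, so the analysis set is chosen partly by the outcome it is meant to explain.

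**Working it through.** **Step 1. Schedule against treatment length.**

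Inputs: samples at 0, 24, 48 and 72 hours ({8}, Table 2); corticosteroid for 10 days = 240 hours ({11a}); shortest antibiotic course 7 days = 168 hours ({11a}).

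- Share of the corticosteroid course elapsed at the last sample: 72 / 240 = 30%. Time remaining: 240 − 72 = 168 hours = 7 days.
- Against the shortest antibiotic course: 72 < 168 hours, so the last sample is also on treatment in the control arm.
- Taking the enrolment sample as drawn before the first corticosteroid dose, the count is one before, three during and none after treatment.

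**Step 2. Schedule against length of stay.**

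Enrolment at *e* hours after admission, with *e* from 0 to 48, puts the last draw at *e* + 72, that is 72 to 120 hours after admission. The median stay is 4 × 24 = 96 hours. A participant enrolled at 24 hours reaches the last draw exactly at the median stay; one enrolled at 48 hours reaches it a day later.

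**Step 3. Share gone before the 72-hour draw.**

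The documents give only the median stay, so the distribution is assumed: exponential, or log-normal with log-SD σ of 0.5, 0.8 or 1.0, each with median 96 hours. A participant must be in hospital to be enrolled, so the share that has left, alive or dead, is

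[F(*e* + 72) − F(*e*)] / [1 − F(*e*)].

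For the exponential this is 1 − 0.5^(72/96) = 0.41 at any *e*. For the log-normal, F(*t*) = Φ(ln(*t*/96)/σ). Example with σ = 0.5 and *e* = 24: F(96) = 0.500 and F(24) = 0.003, giving 0.497/0.997 = 0.50.

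| Enrolled at | Exponential | σ = 0.5 | σ = 0.8 | σ = 1.0 |
|---|---|---|---|---|
| 0 h | 41% | 28% | 36% | 39% |
| 24 h | 41% | 50% | 48% | 45% |
| 48 h | 41% | 64% | 52% | 46% |

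At mid-window enrolment the range is 41% to 50%. The full range, 28% to 64%, needs every participant enrolled at one end of the window.

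**Step 4. Why early deaths count.**

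At the mortality assumed in Sample size {14}, expected deaths by day 30 among 50 per arm are 50 × 0.20 = 10 (control) and 50 × 0.15 = 7.5 (intervention). With so few deaths, each one without a 72-hour sample removes about a tenth or more of its group from a complete-series analysis.

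**Step 5. The same check at 24 hours.**

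Replacing 72 by 24 in the formula gives 0.3% to 16% gone if enrolled at admission, 8% to 18% at 24 hours and 16% to 22% at 48 hours. Loss is smaller at the 24-hour draw but not absent.

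**The case against.** The strongest reply is that this is loose wording in a laboratory section. The secondary objective ({7}, {12}) asks about pre-existing and treatment-induced changes and claims no after-treatment state. The model in {20a} is limited to 72 hours and fits the schedule. The plasma sentence in {33} has no separate during category and can be read as before and after starting treatment, which a 24-hour sample satisfies. All of that stands. It does not rescue the transcriptome and cell-phenotype sentences, which list during and after as separate states.

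On missing samples, the reply is that no section reports any missingness, that the stay distribution is assumed, and that a mixed model can use incomplete series. That also stands. But {20a} sets a complete-case rule for secondary endpoints, this is one of them, and the text does not say which governs the serial samples. Section {20c} promises losses by group at each time point, but defines them as defaulters and withdrawals, not as deaths or discharges.

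A reader might go further and infer three things the documents do not support:

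- That the third secondary objective cannot be met. It can, as early on-treatment change.
- That the 72-hour sample is known to be missing according to outcome, or differently by arm. This is an inference from the design; no rate is stated, and an arm difference would need corticosteroids to alter time to discharge or death.
- That a baseline-to-24-hour contrast should become primary. By Step 5, up to 22% may already have left by then, and recruitment ended on 30 June 2024, so this would demote the stated 72-hour analysis after recruitment had closed.

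**Conclusion.** The point holds in two parts of different certainty. The contradiction is certain from the text: {33} promises an after-treatment comparison, and none of the four planned samples falls after treatment. An incidental sample from someone who stopped the drug early would not change that.

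The selection problem is a reasoned inference. It rests on the empty after-discharge cell in Table 2, the 4-day median stay applying to sub-study participants, the assumed stay distributions, and the complete-case rule being applied to the serial samples. On those assumptions, a substantial share, roughly 40% to 50% at mid-window enrolment, could lack the 72-hour sample.

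The consequence is confined to a sub-study of about 100 of 2,180 participants. The sample size and the primary mortality analysis are not touched. It should be corrected because it limits what the sub-study can claim and the correction is cheap.

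**What to change.** 1. In {33}, replace the after-treatment wording for transcriptome, cell phenotype, plasma proteins and metabolites with early on-treatment (up to 72 hours), matching {20a}. State that no conclusion will be drawn about the state after treatment.
2. In {20a}, say that the omics mixed model uses all available samples and is exempt from the complete-case rule for secondary endpoints.
3. Report by arm, at 24, 48 and 72 hours, how many samples were lost to death and how many to discharge.

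Leave the objective in {7} and {12} and the 72-hour window as they are.

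The cost is wording and a small table; no new samples are needed. The downside is a narrower claim. Using all available samples reduces selection by early death or discharge but does not remove it, and the report should say so.
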